### Interim Analysis

An interim analysis will be performed after enrolling 40 CP recipients and 40 PS-matched controls. A similar statistical analysis will be performed as previously described.

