### Time of the Study

The proposed duration of 3 months was considered ideal for recruiting the first 40 CP recipients for our proposed prospective study. If interim analysis shows the benefit of CP, we will increase the sample size and extend the trial period.

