### Study Population

A total sample size of 575 patients, 115 CP recipients and 460 matched controls (1:4 ratio), will be sufficient to detect a clinically important difference of 11.6% between two groups (CP recipients vs matched controls) in 30-day mortality using a two-tailed *z* test of proportions and chi-square test with 80% power and a 5% level of significance. This 11.6% difference represents a 12.4% mortality in the CP recipient group and 24.4% mortality in the matched control patients [23].

The treatment group (CP recipients group) will have 115 patients who have COVID-19 but have not recovered yet as per the inclusion criteria. The control group (comparator group) will have 460 patients who are either not consenting to receive CP or those who will not be able to receive CP due to nonavailability to compare the efficacy of the CP. Control group patients will be subjected to propensity score (PS) matching based on age, gender, diabetes mellitus (DM), hypertension (HTN), and intubation.

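### The interim comparison is set at one matched control per recipient although the design matches four, with no reason given, which costs precision wherever more matches are available

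*Protocol article*

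**What the plan says.** Study Population in the protocol article fixes the main comparison: "A total sample size of 575 patients, 115 CP recipients and 460 matched controls (1:4 ratio". The Abstract gives the same numbers. The controls are patients who declined CP or for whom none was available. They are matched by propensity score on age, gender, diabetes, hypertension and intubation.

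The Interim Analysis section then says: "An interim analysis will be performed after enrolling 40 CP recipients and 40 PS-matched controls". It continues: "A similar statistical analysis will be performed as previously described". The article gives no reason for moving from four controls per recipient to one. Where the Abstract and Results mention comparators for the first 40 recipients, they give no ratio.

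Time of the Study attaches a consequence to this look: "If interim analysis shows the benefit of CP, we will increase the sample size and extend the trial period".

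**The concern.** Two analyses of the same endpoints are built with different matching ratios, and the less precise ratio belongs to the look on which expansion depends. Recipients are the scarce group. Controls are untreated patients, and the article's Data Collection section has clinical information retrieved from hospital records. Where a recipient has two, three or four suitable controls by then, using only one widens the interval for no stated gain. A real benefit is then somewhat more likely to go unseen when the sponsor decides whether to enlarge the trial.

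**Working it through.** **Inputs**
- Interim numbers: 40 recipients and 40 controls (Interim Analysis).
- Design ratio: 1:4 (Study Population). For 40 recipients this would mean 4 × 40 = 160 controls.
- 30-day mortality: 12.4% with CP and 24.4% in controls (Study Population).
- Two-sided 5% level (Study Population, Statistical Analysis).
- ICU length of stay is the primary efficacy endpoint (Study Endpoint and Outcome Measures). The article gives no SD or target effect for it, so effects of 0.3 and 0.5 SD are my assumption.
- All calculations treat the groups as independent, as the article's own sample size does.

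**The plan's own figure.** The two-sided pooled z test with four controls per recipient needs, in the recipient group,

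n = [1.96·√(p̄(1−p̄)·1.25) + 0.842·√(p₁(1−p₁) + p₂(1−p₂)/4)]² / (p₂−p₁)²

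- For 12.8% against 24.4%, the stated 11.6-point difference, p̄ = 0.2208 and n = 114.9. This gives 115 + 460 = 575, as stated.
- For the printed rates, 12.4% against 24.4%, the difference is 12.0 points and n = 106.6, so 107 + 428 = 535.

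The formula therefore reproduces the plan. The mismatch between 11.6 and 12.0 points is a separate matter. I use the printed rates below and check the others.

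**Interim standard error for mortality**, SE = √(p₁(1−p₁)/n₁ + p₂(1−p₂)/n₂)
- 40 against 40: √(0.124·0.876/40 + 0.244·0.756/40) = 0.0856, 95% half-width 16.8 points.
- 40 against 160: √(0.124·0.876/40 + 0.244·0.756/160) = 0.0622, 95% half-width 12.2 points.

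**Interim power for mortality**, Φ[(0.120 − 1.96·SE₀)/SE], where SE₀ is the pooled standard error
- 40 against 40: SE₀ = 0.0866, Φ(−0.582) = 28.0%.
- 40 against 160: SE₀ = 0.0732, Φ(−0.378) = 35.3%.

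| Controls | SE (points) | Power |
|---|---|---|
| 40 | 8.6 | 28.0% |
| 80 | 7.1 | 32.1% |
| 120 | 6.5 | 34.1% |
| 160 | 6.2 | 35.3% |

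With 12.8% against 24.4%, power is 26.3% at 1:1 and 33.0% at 1:4. The gain is limited because extra controls do not add recipients: about 40 × 0.124 = 5 recipient deaths are expected under either ratio.

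**Continuous endpoint, equal variances**, SE in SD units = √(1/n₁ + 1/n₂)
- 40 against 40: √0.0500 = 0.2236.
- 40 against 160: √0.03125 = 0.1768.
- Ratio: √(0.03125/0.0500) = 0.79, so the SE is about 21% smaller at 1:4.

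Power is Φ(effect/SE − 1.96):

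| Assumed effect | 40 against 40 | 40 against 160 |
|---|---|---|
| 0.3 SD | 27% | 40% |
| 0.5 SD | 61% | 81% |

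**The case against.** The strongest reply is that the section sets a trigger and does not order any controls to be dropped. A reader might infer that three quarters of the controls are thrown away. The article does not support that: 460 is an end-of-study total, and nothing says that four matches per recipient will be in hand at the 40th recipient. Scarcity is plausible. The Abstract warns that exactly matched controls may not be found, Statistical Analysis enforces exact matching on the predictors, and the look comes after about three months. This part of the reply stands, and it is why the fix should be worded as up to four available matches.

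Three further points also stand.
- A lower ratio at an interim look is permissible and does not bias the estimate. A reader might infer that interim and final results cannot be compared. They can, through their confidence intervals.
- A reader might infer that this look decides whether the trial continues. The text says only that a benefit leads to a larger and longer trial. It gives no stopping rule.
- The ratio is not the main limit on this look. The article does not define benefit, and mortality power is low either way.

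The reply that 1:1 is simply a trade of precision for closer matches is weaker. The sponsor has already accepted 1:4, and exact matching on the predictors means that second to fourth matches should lose little closeness.

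**Conclusion.** The point holds as an unexplained loss of precision. It is neither a contradiction nor a bias. If four matches per recipient were available, the 1:1 cap would raise the standard error of the mortality difference from 6.2 to 8.6 points and lower power from about 35% to 28%. For a continuous endpoint the standard error would be 0.2236/0.1768 = 1.26 times as large. These are upper bounds on the loss. With two matches per recipient on average, the mortality standard error is 7.1 points and power 32%. If only one match per recipient exists, nothing is lost.

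The mortality figures rest on the article's own rates. The ICU-stay power figures rest on assumed effects and should be read as a range. More controls would improve the look but would not make it well powered for mortality.

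**What to change.** Reword the Interim Analysis section along these lines: *The interim look takes place once 40 CP recipients and at least 40 matched controls are in. It uses every matched control then available, up to four per recipient, selected by the rule of the final analysis and weighted for the varying number of matches.* If there is a reason to hold the look to one control per recipient, state it instead.

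No further recipients are needed. Up to 160 − 40 = 120 control records would have to be retrieved earlier, and the final analysis needs them anyway. The look may wait briefly for data entry. Keeping 40 controls as the minimum prevents a shortage of matches from holding it up.

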### Statistical Analysis

Descriptive and inferential statistics will be used to characterize the study sample and test the hypotheses. Descriptive results for all quantitative variables such as age will be presented as mean (SD; for normally distributed data) or median with interquartile range (for data not normally distributed), while numbers (percentage) will be reported for all qualitative variables such as gender.

To assess the independent effect of CP transfusion safety and survival, we will conduct a PS-matching (based on age, gender, DM, HTN, and intubation) analysis. Among the predictors, exact matching will be enforced to achieve the balance for all predictors between the plasma and control groups.

The bivariate analysis will be performed using independent sample *t* test, Mann-Whitney *U* test, Pearson chi-square test, or Fisher exact test whenever appropriate to compare the demographic characteristics (eg, age, gender, nationality) and clinical characteristics (improvement in oxygenation, laboratory parameters, radiological findings, complications, and length of hospital stay) between those who will receive the CP and those who will not receive this therapy.

The multiple binary logistic regression model will be used to assess the effect of CP transfusion on 30-day mortality after adjusting for potential confounding factors compared to matched controls patients. The adjusted odds ratio and 95% confidence interval for the adjusted odds ratio will be reported. The Hosmer-Lemeshow goodness-of-fit statistics will be used to determine whether the model adequately describes the data.

The time-to-event analysis will be measured from the date of diagnosis. The overall survival at 30 days and 3 months will be evaluated using the Kaplan-Meier estimator and compared between the two groups (plasma recipients vs matched control patients) using the log-rank test. A Cox proportional hazard model will also be used to estimate the hazard ratio for in-hospital 30-day mortality for the plasma group compared with matched control group patients after adjusting for potential confounding factors. In addition, interactions between CP administration and all the predictors will be tested to see if the plasma effects will be the same in subgroups. A *P*<.05 (two-tailed) will be considered statistically significant. All statistical analyses will be performed using SPSS version 24 (IBM Corp).

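### The interim carries the full adjusted mortality models and interaction tests to 40 versus 40 patients, where about 15 deaths are expected: too few for a reliable adjusted estimate and often too few to fit the interactions

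*Protocol article*

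**What the plan says.** The Interim Analysis section sets one look, at 40 plasma recipients and 40 propensity-matched controls, and gives its method in one sentence: "A similar statistical analysis will be performed as previously described".

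The Statistical Analysis section supplies what is carried over. For mortality it states: "The multiple binary logistic regression model will be used to assess the effect of CP transfusion on 30-day mortality after adjusting for potential confounding factors". It adds an adjusted Cox model for in-hospital 30-day mortality and, in the same paragraph, tests of interaction between plasma and every predictor. The adjusters are not listed. The only predictors named are the five matching variables: age, sex, diabetes, hypertension and intubation.

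The Study Population section gives the planning rates, "12.4% mortality in the CP recipient group and 24.4% mortality in the matched control patients".

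On the use of the interim, Time of the Study says: "If interim analysis shows the benefit of CP, we will increase the sample size and extend the trial period". The Results and Conclusions parts of the abstract, and the main Results section, commit to sharing or publishing the interim findings.

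**The concern.** The models in the Statistical Analysis section are sized for the final sample of 575, where well over 100 deaths are expected. The interim has 80 patients and, at the plan's own rates, only about one ninth of those deaths.

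With so few events per estimated effect, ordinary maximum likelihood has three weaknesses. Estimates are very imprecise. When there is a real effect, they are pushed away from the null on average. In some samples the fit breaks down because a combination of covariates separates deaths from survivors. Interaction terms make this much worse, because they split about 5 expected deaths in the plasma group across subgroups.

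The interim results are to be made public and may bear on whether the trial is enlarged. An inflated adjusted odds ratio, or an interaction estimate from a fit that has broken down, could be read as evidence. The problem comes from the interim sentence alone and does not need incomplete follow-up to arise.

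**Working it through.** **The plan's own sample size.** Inputs from Study Population: "detect a clinically important difference of 11.6% between two groups", 1:4 allocation, "chi-square test with 80% power and a 5% level of significance". Taking 24.4% in controls and 24.4 − 11.6 = 12.8% with plasma, the pooled proportion is (0.128 + 4 × 0.244)/5 = 0.2208. The two-sided pooled-variance formula gives

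n(plasma) = [1.96 × √(0.2208 × 0.7792 × 1.25) + 0.8416 × √(0.128 × 0.872 + 0.244 × 0.756/4)]² / 0.116² = 1.2432² / 0.01346 ≈ 114.9, i.e. 115.

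With 4 × 115 = 460 controls the total is 575, as stated. The printed 12.4% and 24.4% differ by 12.0 points, not 11.6. That is a separate inconsistency and hardly changes the count below.

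**Expected deaths.**

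| | Plasma | Control | Total | Per effect, 6 | Per effect, 11 |
|---|---|---|---|---|---|
| Interim 40 + 40 | 40 × 0.124 = 4.96 | 40 × 0.244 = 9.76 | 14.7 | 2.5 | 1.3 |
| Final 115 + 460 | 115 × 0.124 = 14.3 | 460 × 0.244 = 112.2 | 126.5 | 21.1 | 11.5 |

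Six effects means plasma plus the five named predictors. Eleven adds one interaction for each predictor. With 12.8% in place of 12.4% the interim total is 5.12 + 9.76 = 14.9. The 95% range for interim deaths is about 8 to 22.

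**Simulation of 40 versus 40 exactly matched patients, maximum likelihood.** The documents supply the arm sizes and mortality rates. Covariate prevalences and strengths are assumptions, varied over several settings: binary prevalences of 30–70%, intubation log odds ratio 0.7 to 2.5.

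- *Six-effect logistic model.* With a true conditional odds ratio of 0.40 (log −0.917), the mean log odds ratio was −1.07 to −1.10, i.e. 1.17 to 1.20 times the truth. Across three prognostic strengths, with marginal mortality held at the plan's rates, the factor was 1.17 to 1.21. Between 3% and 7% of fits failed. The upper 95% limit was typically 13 to 22 times the lower. Some 28–34% of results were significant, and those had a median odds ratio of 0.12–0.18 against true values of 0.33–0.43.
- *Six-effect model, no plasma effect.* Median odds ratio 1.00, with about 5% significant.
- *Six-effect Cox model.* 4% failures; mean log hazard ratio 1.09 times the truth.
- *All five interactions jointly.* 51–68% of logistic fits and 59% of Cox fits failed.
- *One interaction at a time.* 17–32% of fits failed, depending on the binary predictor.
- *Firth-penalised six-effect logistic model.* Mean log odds ratio −0.925 against −0.917, about 1% off, with no failures.
- *Final size, 115 + 460, ordinary six-effect model.* Mean −0.949 against −0.917, about 3.5% off, with no failures.

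The fault is therefore specific to the interim.

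**The case against.** A reader might infer that this odds ratio drives the expansion decision. The article does not say so. Time of the Study refers only to benefit, with no outcome, model or threshold. The primary efficacy endpoint is ICU length of stay, and 30-day mortality is secondary. The most that can be said is that an adjusted mortality estimate may inform the decision.

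A reader might also infer that the interim odds ratio cannot be estimated. The simulations do not support that. The six-effect model can be fitted in about 93–97% of samples, its confidence intervals cover at about 96%, and it is unbiased when plasma has no effect. Interval ratios of 13 to 22 correspond to a standard error of ln(13)/3.92 = 0.65 to ln(22)/3.92 = 0.79, so a bias of 0.15 to 0.18 is about a quarter of a standard error. Imprecision is the larger fault. The planned 95% interval would show it, and Firth's penalty would not remove it.

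Three further objections have force. The covariate set is inferred, because the article lists no adjusters. The text does not say that interactions are fitted jointly, although testing them singly still fails often. And "A similar statistical analysis will be performed as previously described" promises a similar analysis, not an identical one, so a shorter model is possible and an unseen analysis plan might give it. Kaplan–Meier curves with a log-rank test, which need no covariates, would also be available.

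What remains is that the article makes a positive statement of method for the interim, names no reduction, and thereby carries over models that suit 575 patients and not 80.

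**Conclusion.** The point holds in limited form. At the plan's own rates the interim offers about 15 deaths, or 2.5 per effect for a six-effect model. The adjusted mortality estimate would be very imprecise and, if plasma works, inflated by about 17–21% on the log-odds scale, with 3–7% of main-effects fits failing. Interaction tests would often be non-estimable: about 50–70% of fits if joint, and roughly 17–32% for each binary predictor if tested singly.

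The event count rests on the documents alone. The number of effects assumes that the five matching variables are the adjusters; more confounders would worsen the ratio and fewer would ease it. The inflation and failure rates rest on assumed covariate distributions and strengths. The final analysis is not affected.

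**What to change.** Replace the method sentence in Interim Analysis with wording such as:

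*At the interim, plasma-by-predictor interactions will not be tested. The effect of plasma on 30-day mortality will be estimated by Firth-penalised logistic regression, and by a penalised Cox model for time to death, each with plasma and the five matching variables, and reported with its 95% confidence interval. Any odds ratio from a model with plasma alone will be labelled unadjusted and secondary.*

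One estimator should be fixed in advance, not a choice between the penalised and the plasma-only model, because the two target different quantities. The plan's rates give an unadjusted odds ratio of (0.124/0.876)/(0.244/0.756) = 0.44, whereas the adjusted value used in the simulation was 0.40. Leave the final analysis unchanged.

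The cost is small. A penalised routine may be needed outside the planned SPSS set-up, and fewer interim results will be nominally significant (about 25% instead of 30% in simulation). The penalised logistic model was simulated; the penalised Cox model was not, and is proposed by analogy. The change makes the estimate more stable but does not make 15 deaths informative, so the interval should be reported as prominently as the estimate.

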### Monitoring and Safety

Plasma infusion is a routine practice in health care facilities. All known adverse events and SAE of CP infusion, such as anaphylaxis, TRALI, and TACO, will be collected as per the SFDA reporting standard. SAE or death of a study participant due to any cause will be reported by the study team to the IRB chairman and principal investigator within 24 hours of the event.

### Confidentiality Statement

All subject-related personal information will be saved in password-protected files, which will only be accessed by the study research team. All data will be archived in our archiving facility within the hospital once the study has come to an end. This will be in accordance with the standard requirement for the clinical trial archival.

### Patient and Family Education, and Donor Recruitment Strategy

A variety of methods will be used to recruit CP donors for the study. These include referrals of the recovered patients from various hospitals, dissemination of messages to the public through social media platforms, and a website set up specifically for the study for general information and communication [24].

We will be using the following Twitter account: @Plasma4CovidKSA for public information only. Approved videos will be used on the website and Twitter account. In addition, multilingual advertisement statements and links to the videos by international physicians may be shared with non-Arabic speaking patients. Detailed bilingual ICFs approved by the MOH and IRBs will be used for both CP donors and CP recipients.

## Results

We are still collecting data and recruiting patients for our ongoing national clinical trial. We will soon share the results of an interim analysis of the first 40 CP recipients and PS-matched controls. Once the study is completed, the final results will be published.

The following approvals have been obtained in addition to IRB approvals of the participating centers: MOH Central IRB log No 20-COVID-19-01M (approved on April 2, 2020); SFDA Saudi Clinical Trials Registry No 20041102 (approved on April 14, 2020); and the ClinicalTrials.gov identifier is NCT04347681 (updated and under process).

## Discussion

The study of the Saudi population at risk of severe COVID-19 has some distinct features, as Saudi Arabia was recently challenged by related coronaviruses including MERS-CoV that might lead to distinct immunological responses to SARS-CoV-2. The intention overriding the scientific merit of a randomized controlled trial during this pandemic is an attempt to add CP in the armamentarium against COVID-19, as this readily available agent has historically shown benefit in the treatment of related coronaviruses. There are multiple theoretical and scientific reasons to support our thinking that CP may turn out to be an effective treatment. However, the bottom line is that we do not have enough data to be certain. CP trials that have been published so far have limitations and conflicting data. Our group and others are working hard during this time to establish evidence that could support the therapeutic use of CP for patients with COVID-19.

Limitations of our study include, first, the design of the study, as we could not find it feasible to make the study a randomized controlled trial with our patient population due to the strong perceived benefit of CP in the minds of the patients and treating physicians in this situation. Second, our collaborating centers are of various levels from secondary to tertiary care hospitals with limitation of experience uniformity in conducting such a collaborative study. However, we intend to be a mutually supportive group and keep our study elements uniform. In addition, currently, anti–SARS-CoV-2 antibodies titration facilities are not available countrywide in Saudi Arabia. However, we plan to save aliquots of collected convalescent plasmas to test antibody titers whenever such facilities will be available. Last, we could not include the investigation of some biomarkers like interleukin-6 during treatment in our protocol, due to nonavailability in some centers. Nonetheless, treatment with CP seems promising to treat patients with COVID-19, and a national clinical trial to explore the efficacy and safety of CP is justified.

